## Abstract

Unhealthy diets represent a major risk for the pathogenesis of metabolic and chronic inflammatory diseases. Improving the quality of diet is important to prevent chronic diseases, and diet-induced modifications of the gut microbiota (GM) community likely play an important role. The EU-funded Stance4Health project aims at performing a randomized clinical trial based on a nutritional intervention program in the context of normal weight and overweight adults as well as children with obesity and gluten-related disorders or allergy/intolerance to cow’s milk. The trial will evaluate the efficacy of a Smart Personalised Nutrition (SPN) service in modifying GM composition and metabolic function and improving consumer empowerment through technology adoption.

## 1. Introduction

Worldwide, almost one in three people does not have access to an adequate diet and suffers from at least one form of malnutrition: undernutrition, overweight or even obesity, and diet-related non-communicable diseases (DR-NCDs) [1]. In the last decades, the industrial handling of foods and the excessive consumption of processed and ultra-processed foods have led to an increase in the consumption of refined sugars and fats, decreasing the amount of dietary fibre [2]. This profound dietary simplification is likely capable of influencing gut microbiota (GM) diversity with consequent unexpected effects on immune and inflammatory responses [1,3]. Mammalian GM has recently been shown to play a role in the pathogenesis of “civilization diseases” such as obesity, cancer, cardiovascular disease, and diabetes [4,5], but also immune disorders such as coeliac disease [6] and food allergy [7]. GM plays a role in the regulation of the host’s energy balance. It enhances the efficiency of the energy harvest from foods and influences the synthesis, bioavailability, and function of nutrients. This activity produces different beneficial metabolites and microbial compounds such as short-chain fatty acids, metabolites of aromatic compounds, and neuro-active chemical substances, acting as signalling molecules for metabolically active organs [8,9].

The close relationship between GM and diet-related diseases suggests focusing research attention on evaluating their interactions to improve human health by modulating the diet [10].

Overweight and obesity, which have nearly tripled globally since 1975, are linked to more deaths worldwide than underweight [11]. Coeliac disease has been increasing worldwide. In Europe, the United States, and Australia, estimates of coeliac disease prevalence range from 1:80 to 1:300 children [12]. IgE-mediated food allergy affects up to 10% of the European population, and the prevalence is higher among children than among adults [13]. It represents a growing and threatening public health concern that can significantly impact the quality of life of children and their families [14]. In this context, a personalized approach based on differential responses to foods or nutrients that takes into account different genotype or phenotype characteristics, eating behaviours, and personal preferences could be more effective in changing habits and improving health status than a conventional one-size-fits-all intervention.

The Stance4Health project aims at designing a randomized clinical trial that will be used to validate and evaluate the efficacy of a Smart Personalised Nutrition (SPN) service in modifying GM composition and metabolic function and improving consumer empowerment through a technology adoption. The trial will be implemented in the context of normal weight and overweight adults as well as children with obesity and gluten-related disorders or allergy/intolerance to cow’s milk. The SPN service will be delivered to consumers through the nutritional software mobile app i-Diet Stance4Health, a wearable wrist band, capable of measuring daily activity, and the tailored production and delivery of foods for individuals or specific groups of the population (i.e., healthy adults, people with food allergies, coeliac disease, obesity, and overweight).

## 2. Materials and Methods

### 2.1. Study Design

The multicentre single-blind, placebo-controlled, randomized trial will be conducted in Oviedo by the University of Granada, Spain, at the Technische Universität Berlin, Berlin, Germany, at the University General Hospital of Patras, Patras, Greece, at the University Hospital of Ioannina, Ioannina, Greece, and at the University General Hospital “Attikon”, Athens, Greece.

The study design follows the Standard Protocol Items: Recommendations for Interventional Trials (SPIRIT) guidelines. The study is registered with the ISRCTN registry (https://www.isrctn.com/ISRCTN63745549) (accessed on 18 March 2022).

### 2.2. Eligibility Criteria

Five study populations will be included in the study:(1)Apparently healthy adult subjects (both sexes), aged 20–65 years, with a body mass index (BMI) between 20–28 kg/m^2^, stable weight, ability to use a smartphone, and Internet connection availability. Exclusion criteria are the diagnosis of chronic gastrointestinal (GI) disorders, coeliac disease, or chronic diseases such as diabetes or other metabolic diseases; present pregnancy or lactation (<6 weeks before study start), or intention to become pregnant in the next 12 weeks; recent inflammation and/or long-term use of an-ti-inflammatory drugs; medically prescribed diet or specific dietary regimens for any reasons (i.e., high-protein diet, vegetarianism, veganism, etc.); antibiotic treatment (<3 months before study start); intake of antioxidant, pre- or probiotic supplements (<1 month before study start); intense physical activity (>10 h/week); alcohol consumption >21 drinks/week for men and >14 drinks/week for women.(2)Normal weight children (of both sexes), aged 6–11 years, with a BMI >5th and <85th percentile for age, gender, and height. Exclusion criteria are the diagnosis of chronic GI disorders and any other chronic disease, elimination diet, intake of probiotics (<2 weeks before study start).(3)Children (of both sexes) with obesity, aged 6–11 years, with a BMI ≥95th percentile for age, gender, and height. Exclusion criteria are the diagnosis of chronic GI disorders and endocrinopathies, intake of probiotics (<2 weeks before study start).(4)Children (of both sexes) with gluten-related disorders, aged 6–11 years, diagnosed with coeliac disease or wheat allergy (sIgE), on elimination diet. The exclusion criteria are the absence of symptoms.(5)Children (of both sexes) with allergy/intolerance to cow’s milk, aged 6–11 years, with an IgE-mediated milk allergy on an elimination diet from infancy, lactose intolerance (symptoms plus breath hydrogen positive test), overgrown IgE-mediated milk allergy but current aversion for milk, or nondefinable phenotype (children who avoid milk but do not belong to any of the previous phenotypes). Exclusion criteria are the diagnosis of other GI comorbidities.

### 2.3. Intervention Study and Mobile App i-Diet Stance4Health

This study will be a multicentre (five recruiting centres), parallel group randomised controlled trial, characterised by the use of the nutritional software mobile app i-Diet Stance4Health (Figure 1). A statistical model was developed to predict nutrients that must be incorporated into the diet of participants to transform their gut microbiota back into a healthy state, close to that of normal weight subjects. Based on the statistical model, the i-Diet Stance4Health app will suggest food choices in retailers and give participants specific advice about nutrition and lifestyle (taking into account or not GM composition, respectively for treated or control groups). The app will generate personalised diets (breakfast, lunch, dinner, snacks) based on Mediterranean dietary patterns encouraging fruits, vegetables, and whole grains consumption which are foods rich in compounds that have been shown to have positive effects on GM composition [15]. Tannins pills will supplement the diet since they have proven effective in modifying GM composition and functionality [16]. Participants’ health status, objectives, and habits (desired daily intakes, dishes that make up these intakes) will also be considered. The i-Diet Stance4Health will be used as a novel tool to record food intake (dietary assessment). To do so, participants, or parents in the case of children, will learn how to use the app through specific instruction/training. Specifically, they will indicate which serving size they usually prefer by pointing to it in the set of photographs to facilitate the estimation of the portion size. The users will also have the opportunity to make variations in the proposed menu. The app will estimate menus taking into account the nutritional values of foods and recipes by using a food composition database specifically developed in the framework of the Stance4Health project [17]. After a 2-week run-in period, the eligible participants will be randomly assigned to a 12-week intervention with two different levels of personalised nutrition: Level 1 and Level 2.

Level 1 (entry-level) intervention will consist in the use of i-Diet Stance4Health and the analysis of GM and metabolites. Level 2 (advanced level) will consist of the use of i-Diet Stance4Health and the analysis of GM and metabolites (as in the entry level), plus the use of a wearable wrist band only in adults, a metabolomics test to check the presence of metabolism disorders [18,19], and the intake of tannins extracts in pills for adults and in biscuits for children (treated group) or placebo (control group). The wearable band will be used to record physical activity, heart rate, blood pressure, and body composition as well as to refine food intake. Tannin extracts will be produced and distributed looking for a deeper modulation of the GM [16]. All data recorded in i-Diet Stance4Health and by the wearable band and results of the analyses will be recorded in specific databases. In detail, 200 Spanish and German adults will follow the entry-level intervention, and 200 will follow the advanced level intervention, equally divided into control and treated groups. The same criteria will be used for 400 Greek children (100 normal weight, 100 with obesity, 100 with gluten-related disorders, and 100 with allergy/intolerance to cow’s milk). Among them, half will be included in Level 1 and half in the Level 2 intervention.

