## 3. Results

The overall objective of Stance4Health is to promote the adoption of personalised nutrition based on the use of smart mobile technologies as well as tailored food production, which will optimize GM activity. A set of new instruments developed within the project will allow for the adoption of healthy, pleasant, and sustainable dietary patterns based on the principles of the Mediterranean Diet, while also encouraging citizen engagement for an improved understanding of a healthy lifestyle. The nutritional intervention proposed here will test the efficacy of the SPN service developed by the Stance4Health project in promoting a healthy and environment-friendly lifestyle. The SPN service will be delivered to consumers through different tools such as the nutritional mobile app i-Diet Stance4Health, wearable wrist bands to measure daily activity, and production and delivery of food supplements and fortified foods for individuals or specific groups of the population (e.g., people with allergies, obesity, etc.).

To date, no studies are available that evaluated the effects of a SPN service based on the use of a nutritional app. It will allow a more personalised service to achieve better use of time, which is a benefit for the nutrition specialists and for consumers/patients.

The trial results will be important to understanding if the SNP service proposed by Stance4Health will be capable of ameliorating the intestinal microbiota and empowering consumers to make healthy and sustainable dietary choices.

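### The stated aim is the efficacy of the SPN service, but every arm uses the app, so the randomised contrasts test only GM-informed advice (Level 1) or that advice plus tannins (Level 2)

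*Protocol article*

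**What the plan says.** **Aim.** The Introduction says the trial will be used to "validate and evaluate the efficacy of a Smart Personalised Nutrition (SPN) service in modifying GM composition and metabolic function". The Results section repeats this: "The nutritional intervention proposed here will test the efficacy of the SPN service developed by the Stance4Health project".

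**The service.** The Introduction describes its delivery: "The SPN service will be delivered to consumers through the nutritional software mobile app i-Diet Stance4Health, a wearable wrist band", together with tailored foods. The Results section extends the last item to food supplements and fortified foods.

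**The arms (Section 2.3).** The app gives advice to both groups, "taking into account or not GM composition, respectively for treated or control groups". For the lower level, "Level 1 (entry-level) intervention will consist in the use of i-Diet Stance4Health and the analysis of GM and metabolites". Level 2 keeps all of that, "plus the use of a wearable wrist band only in adults, a metabolomics test to check the presence of metabolism disorders", and then "the intake of tannins extracts in pills for adults and in biscuits for children (treated group) or placebo (control group").

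**Allocation and analysis.** Section 2.7 randomises participants to a level and then to treated or control. Section 2.6 frames the sample size on control versus treated. Section 2.18 gives paired t-tests within each group and independent-sample t-tests on the absolute change.

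**The concern.** The aim speaks of the service as a whole, whereas the comparisons that randomisation protects concern increments on top of an app that everyone uses. Section 2.3 says the app builds Mediterranean-pattern menus from foods thought to benefit the microbiota, and does not limit this to the treated group. Both groups therefore receive something expected to move alpha diversity, the primary endpoint.

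Two conclusions are at risk:

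- A null treated-control difference could be reported as failure of the service, although it is compatible with an app that works equally well in both groups.
- A positive Level 2 difference could be reported as success of personalised advice, although the protocol itself adds tannins for their effect on the microbiota: "Tannin extracts will be produced and distributed looking for a deeper modulation of the GM".

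Consumer empowerment through technology adoption is also part of the aim. Because every arm has the technology, its effect on that outcome has no randomised comparator.

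**Working it through.** **Step 1. Contents of the four arms (Section 2.3).** The sentence on GM-informed advice is not limited to one level, so I apply it to both.

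| Arm | App | Advice uses GM | Band (adults), metabolomics test | Tannins or placebo |
|---|---|---|---|---|
| Level 1 control | yes | no | no | neither |
| Level 1 treated | yes | yes | no | neither |
| Level 2 control | yes | no | yes | placebo |
| Level 2 treated | yes | yes | yes | tannins |

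**Step 2. What each contrast estimates.**

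- Level 1, treated minus control: the effect of GM-informed advice, given the app.
- Level 2, treated minus control: GM-informed advice and tannins together, given the app, the band (adults) and the metabolomics test. The placebo controls for the tannins, not for the difference in advice.
- Any other pair of arms: the app is on both sides. No pair compares the service with its absence.
- Paired t-test within one arm: change over 12 weeks with no comparator. It mixes any service effect with time, run-in, regression to the mean and study participation.

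**Step 3. The plan's own sample size.** Section 2.6 gives 200 adults per level, and Section 2.3 splits them equally, so there are 100 per arm within a level. Children follow the same criteria: 400 in all, half in each level, hence 100 per cell when the four populations are pooled. The protocol gives no SD, so the figure can only be solved backwards. I assume a two-sided 0.05 level, since sidedness is not stated.

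- Detectable difference = (1.96 + 0.84) × SD × √(2/100) = 2.80 × 0.1414 SD = 0.396 SD, about 0.40 SD.
- If this equals the planned 25%, the implied SD is 25 / 0.396 = 63% of baseline. With a one-sided test it would be 25 / 0.352 = 71%.

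**Step 4. Could the tannin part be separated?** Because level is also randomised, one can form (Level 2 treated − control) minus (Level 1 treated − control).

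- Standard error = SD × √(4/100) = 0.20 SD.
- Detectable effect at 80% power = 2.80 × 0.20 SD = 0.56 SD, which is √2 times the within-level figure.

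Conversion to per cent depends wholly on the missing SD. If it lay between 40% and 80% of baseline (my assumption), 0.56 SD would be 22% to 45% and 0.40 SD would be 16% to 32%.

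This interaction equals the tannin effect only if two conditions hold: the band and metabolomics test do not change the effect of the advice, and the advice and tannin effects add. The first is not self-evident for adults, because Section 2.3 says the band also serves to refine food intake.

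**The case against.** **Tannins belong to the service.** The service as described includes tailored foods and, in the Results section, supplements. Level 2 is then a package test, and a package test need not separate its parts. This stands. A reader might infer that the Level 2 comparison is invalidly confounded, but the documents do not support that. The limit is on attribution only.

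**Controls do not get the full service.** Section 2.4 lets controls take up the full functionality afterwards, including GM analysis and supplements, which implies a reduced version during the trial. If the service means the GM-informed version, treated versus control tests its defining feature against an active comparator. This also stands, and it would be wrong to say that controls receive the whole service. It does not create an app-free arm, and the Introduction and Results name no comparator.

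**The analysis may be specified elsewhere.** Section 2.18 does not say which groups the independent t-tests compare, and a level term or interaction may sit in an analysis plan that is not shown. Its absence from an article is not a fault. The gap between aim and arms is different: no analysis plan can supply a missing comparator.

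**Power for a tannin effect was never claimed.** This is correct. The 25% was set for control versus treated, not for a tannin increment. The 0.56 SD shows the precision of an optional contrast, and is not evidence that the trial is underpowered for its stated comparison.

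**Conclusion.** The point holds as a mismatch between the stated aim and what the arms can show. All four arms use the app, so no randomised contrast estimates the service against no service, and the paired tests cannot stand in for one. Level 1 answers whether GM-informed advice adds to the same app. Level 2 answers whether GM-informed advice plus tannins beats app plus placebo, without saying which part is responsible.

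This rests on Section 2.3 as written, with the advice difference applying at both levels. It does not depend on any SD. The only figures, 0.40 SD within a level and 0.56 SD for the interaction, assume 100 analysed per cell, a two-sided 0.05 level and 80% power.

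The design is usable and the randomised contrasts are valid. This should be fixed because it governs the headline conclusion, but it is a matter of wording and does not undermine the trial.

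**What to change.** - In the Introduction and Results (and the matching sentence of the Abstract), restate the objective as two contrasts: GM-informed advice over the same app without it (Level 1), and GM-informed advice plus tannins over app plus placebo (Level 2). Name the control as an active comparator.
- In Section 2.18, state that efficacy conclusions rest on the between-group contrasts within level and that the paired tests are descriptive.
- Make no claim about the service against usual diet or no service, and do not attribute a Level 2 effect to advice or to tannins alone.
- Optionally, report the group-by-level interaction for each age group as a secondary, exploratory estimate of the tannin addition. State both assumptions (no modification of the advice effect by the band or metabolomics test; additive effects) and its lower precision.

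The cost is a few sentences and a narrower headline claim, plus one model term if the option is taken. Recruitment, allocation and conduct stay as they are.

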### 2.4. Participants Timeline

Each intervention period will last 3 months. At the first contact, information about potential participants’ age, sex, anthropometry, dietary habits, health status, and contact details will be collected to select people with the inclusion/exclusion criteria identified for each study population. For this purpose, people will be encouraged to fill in specific questionnaires and return them by hand, by email, or online. Eligible participants will be asked to fill out the informed consent plus a number of questionnaires on their lifestyle, bowel, and dietary habits. Data will be collected using paper or, due to the epidemiological situation produced by the COVID-19 pandemic, online questionnaires [20]. In the latter case, participants will receive a link to open and accept the informed consent and to proceed with the completion of the questionnaires. On the Stance4Health webpage (www.stance4health.com, accessed on 18 March 2022), three different links (buttons) for the different languages (Spanish, German, and Greek) are included to allow participants to fill out the questionnaires online.

Three clinical evaluations of the study populations will be performed: at the beginning (T0), after 6 weeks (T1), and at the end of the interventions (T2) (Table 1). At T0 and T2, health [(blood pressure, previous pathologies, anthropometric (height, weight, waist circumference, fat mass, muscle mass)], dietary (food frequency questionnaires—FFQ), lifestyle (smoking habits, physical activity and sleep patterns), and socioeconomic status information will be collected in specific datasheets. Two FFQs will be used in the study, the FFQ_IDEFICS/i.Family [21] and the FFQ_S4H specifically developed for the study of GM. GM composition and metabolomic profile, and SCFAs and bile acids levels in feces will be assessed three times: at T0, T1, and T2.

At the end of the intervention, participants will have the opportunity to continue using the technologies for free as an incentive not to withdraw from the study. Moreover, all participants can choose to use the full functionality of i-Diet Stance4Health and associated elements (such as GM analysis and the food supplements), even if they were included in the control group. This could be an indicator of the acceptability and utility of the intervention.

### 2.5. Outcome Measures

Variation in GM alpha diversity, which will characterise species diversity change in each individual due to the impact of the intervention, represents the primary end point [22,23]. This end point is determined by 16S rRNA gene-targeted sequencing of microbial DNA isolated from stool samples. For selected samples, shotgun metagenomic and meta-transcriptomic sequencing will be applied.

Besides the changes in GM composition, consumer empowerment through technology adoption and long-lasting adoption of a healthy and sustainable diet are additional relevant outcomes of the intervention study.

The study comprises a number of secondary outcomes including appetite regulation and food intake, anthropometry (body weight, waist circumference, and body composition), blood pressure, physical activity levels, short-chain fatty acids and bile acids in feces, and urine metabolomics.

